#### **4.4 Criteria of Dropout**

Participants included in the study should be classified as dropout (with missing data but not excluded in the analyses) if they meet any of the following criteria:

- ① Lost to follow-up during the study period;
- ② Request to withdraw the informed consent;
- ③ Other circumstances that affect the completion of follow-up visits.

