### **Section 5. Sample Size**

The minimal clinically important difference (MCID) of the primary outcome varies among studies, ranging from 8 to 40 for each subscale among patients with knee injuries or osteoarthritis. Based on the anchor-based method, the MCIDs are 10.7–16.7 for the 4 subscales, averaged 13.8. Therefore, the statistical hypothesis is based on detecting a between-group difference of 13 points. The maximum SD is estimated to be 20 points, thus the effect size is 0.65. With the 2-sided significance level and power setting at 0.05 and 0.9, respectively, a sample size of 51 participants is required in each group (1:1 allocation, calculated using G\*Power 3.1, based on the test of mean difference between two independent groups, and assuming a balanced baseline). After adding the dropout (estimated within 15%), a total of 120 participants (60 in each group) should be included in this study.

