#### ② KOOS subscales, at 3, 6, and 12 months

The MCIDs for KOOS subscales of pain, symptoms, activities of daily living, sports and recreation, and quality of life are 16.7, 10.7, 18.4, 12.5, and 15.6, respectively.

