## **Section 12. Statistical Analysis**

### **12.1 Primary Analysis**

The primary analysis will be performed following the intention-to-treat principle, which emphasizes on the original group allocation by randomization. Specifically, once a participant is enrolled and undergoes randomization, the baseline and outcome measures will be included in the allocated group, regardless of whether the participant violates the protocols and whether the participant is dropout during follow-up: (1) if a participant is randomized to the intervention group but does not receive 3 doses of PRP injection, this participant will not be

excluded from the intervention group; (2) if a participant is randomized to the control group but receives knee injection out of the protocol, this participant will not be excluded from the control group; (3) if a participant is randomized to either group but lost to follow-up, this participant will not be excluded from the primary analysis, either. In principle, the primary analysis should include all participants randomized in this study. For the missing data, simple or multiple imputation will not be performed in the primary analysis.

All statistical analyses will be performed using the IBM SPSS software, with a 2-sided significance level of 0.05. Descriptive statistics will be presented as mean and SD (for normally distributed values), median and interquartile range (for non-normally distributed values), or number and percentage (for categorical variables).

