#### ① Subjective assessments

The primary outcome, KOOS4 at 12 months, has been validated to be associated with knee symptoms and pain at baseline. Referenced to statistical methods in previous studies, an analysis of covariance (ANCOVA) will be performed to analyze the between-group difference using the baseline KOOS4 as the covariate for adjustment. For other subjective assessments included in the secondary outcomes, ANCOVA models will also be applied to analyze the between-group differences with adjustment for the corresponding baseline scores. Between group differences will be presented as mean, 95% confidence interval (CI), and P value. For an outcome with a statistically significant difference, the clinical significance should be evaluated by comparing the mean and 95% CI with the MCID.

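### The primary analysis is described as keeping participants lost to follow-up, but a 12-month ANCOVA without imputation is a complete-case analysis and leaves the 3- and 6-month KOOS unused

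*Protocol*

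**What the plan says.** Four statements in the Protocol bear on who enters the primary analysis.

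- **Section 4.4** defines dropouts as "classified as dropout (with missing data but not excluded in the analyses").
- **Section 12.1**, item (3), says that a randomised participant who is lost to follow-up is not removed from the primary analysis. It continues: "In principle, the primary analysis should include all participants randomized in this study".
- **Section 12.1** then says: "For the missing data, simple or multiple imputation will not be performed in the primary analysis".
- **Section 12.1, Subjective assessments**, fixes the model for 12-month KOOS4: "an analysis of covariance (ANCOVA) will be performed to analyze the between-group difference", with baseline KOOS4 as the covariate.

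Interim data exist. Section 10.2 lists "KOOS subscales, at 3, 6, and 12 months" as a secondary outcome, and the schedule in section 9 agrees. Section 10.1 defines KOOS4 as the mean of four of those subscales, so KOOS4 can be derived at 3 and 6 months.

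Section 12.2 adds a post-hoc sensitivity analysis. When more than 5% of an outcome is missing, multiple imputation by chained equations is run. Its listed variables are arm, age, gender, sports participation, graft diameters, meniscal treatment and the baseline score. No post-operative score is listed.

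**The concern.** An ANCOVA with one outcome per participant cannot use a row in which that outcome is missing. With imputation excluded, and no likelihood-based repeated-measures model named, the promise to keep dropouts in the primary analysis cannot be met. The protocol itself fixes the model, the analysis set and the missing-data rule, so this is not a detail left for a later plan.

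Two things are at stake. The first is labelling: a complete-case result would be reported as an intention-to-treat result on all randomised participants. The second is possible bias. Section 7.2 makes participants aware of their allocation, only one arm is offered injections, and the outcome is self-reported. The reasons for leaving could therefore differ between arms. If leaving follows how the knee is doing at 3 or 6 months, the scores that would allow a correction are on file but enter neither the primary model nor the listed imputation model.

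**Working it through.** **1. The plan's own sample size.** Section 5 gives: "the statistical hypothesis is based on detecting a between-group difference of 13 points"; "The maximum SD is estimated to be 20 points"; "With the 2-sided significance level and power setting at 0.05 and 0.9, respectively".

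- Effect size: 13/20 = 0.65.
- Two-sample t test (noncentral t): power is 0.896 with 50 per arm and 0.902 with 51, so n = 51 per arm. This reproduces the plan's figure.
- Dropout: 51/(1 − 0.15) = 60 per arm, 120 in total. This is also reproduced.

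**2. Who enters the planned ANCOVA.**

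- At 15% missing: 0.15 × 120 = 18 dropped, 102 analysed (51 per arm).
- At 5% missing, the imputation threshold: 0.05 × 120 = 6 dropped, 114 analysed.

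Section 5 therefore already counts on 51 of 60 per arm having data, while section 12.1 speaks of all randomised participants.

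**3. Power.** With 51 per arm it is 0.902, and with 60 it would be 0.942. The dropout allowance does its job, so power is not the problem.

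**4. Size of a possible bias, by hand.** If a fraction d of one arm is missing, and those missing would have scored g points lower than those observed, the observed mean of that arm is too high by d × g. With d = 0.15, g = 10 gives 1.5 points and g = 13 gives 1.95 points.

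**5. Size by simulation.** From the documents: 60 per arm, SD 20, 15% dropout. Assumed, because the documents give no values:

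- true effect 0;
- correlation of baseline with later scores 0.3;
- correlation among post-operative visits 0.5 to 0.8;
- all dropout after month 6, driven by the 6-month score with an odds ratio of 1.8 to 3.3 per SD.

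Results over these ranges (a negative sign understates PRP relative to control):

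| Dropout mechanism | Bias, complete-case ANCOVA | Bias, using 3- and 6-month scores |
|---|---|---|
| Low scorers leave the control arm only; random in the PRP arm | −0.6 to −2.2 | at most about 0.15 in size |
| Low scorers leave control, high scorers leave PRP | −1.4 to −4.3 | at most about 0.15 in size |
| Low scorers leave both arms alike | about 0 (within 0.2) | about 0 (within 0.2) |

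For scale, the standard error of the ANCOVA contrast is about 20 × √(2/51) × √(1 − 0.3²) = 3.8 points.

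**6. Does the imputation in section 12.2 repair this?** As listed, it conditions on arm and baseline variables only. With the other baseline variables taken as unrelated to outcome, imputation on that list gave the same bias as the complete-case ANCOVA: −1.82 against −1.82 in one scenario, −2.10 against −2.09 in another. It would not show the problem.

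**The case against.** The best defence has four parts.

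- **The statements are mainly about group assignment.** Section 12.1 presents intention-to-treat as keeping people in their allocated arm, one sentence is qualified as being in principle, and section 5 openly plans on 51 of 60. This stands in part. The qualification covers only that sentence; item (3) and section 4.4 carry no such reserve.
- **Missing data are not ignored.** Section 12.2 requires numbers, proportions and reasons, and imputation above 5%, which the planned 15% would trigger. This stands, and a reader who infers that the plan has no answer to missing data would be wrong. But that analysis is secondary, and its listed variables omit the interim scores. The list does not forbid adding them.
- **Baseline-adjusted ANCOVA at one visit is a standard method.** True. A reader might infer that it is biased whenever dropout follows an earlier score. That is too strong: with the same mechanism in both arms, the bias in the contrast is about 0.
- **The simulation suits the remedy.** It places all dropout after month 6. The documents give no dropout timing, so it cannot be claimed that most dropouts would have interim scores. Allocation is revealed at the first follow-up visit, which the schedule puts at 4 weeks, and the first post-operative KOOS is at 3 months. A repeated-measures model recovers nothing from the outcomes of people who leave between the two.

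**Conclusion.** The point holds as an internal contradiction and an avoidable weakness. The primary analysis is a complete-case analysis that omits 18 of 120 participants at the planned dropout, while the text says dropouts are kept in.

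Material bias in the treatment contrast is possible, not established. It needs score-related dropout that differs by arm. The open allocation makes that plausible, but nothing in the documents shows that it will happen. Under the assumptions above the bias is about 0.6 to 2.2 points if only low-scoring controls leave, which is 5% to 17% of the 13-point target (0.6/13 and 2.2/13) and below one standard error. It reaches about 4 points, roughly one standard error, only with strong and opposite mechanisms in the two arms. Power is unaffected.

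A reader might conclude that the primary result cannot be trusted unless the model is changed. The documents do not support that. This is a change that should be made, not a fatal defect.

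**What to change.** 1. In section 12.1, make the primary analysis a linear mixed model for repeated KOOS4 at 3, 6 and 12 months, with arm by visit, baseline KOOS4 by visit and an unstructured covariance. The 12-month contrast between arms is the primary estimate.
2. Keep the 12-month ANCOVA as a sensitivity analysis, labelled complete-case.
3. In section 12.2, add 3- and 6-month KOOS4 to the imputation variables.
4. Reword sections 4.4 and 12.1 to state the actual analysis set, for example all randomised participants with at least one post-baseline KOOS4. That set may still leave some people out, so the text should say so and report their number by arm.

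Cost: changes of wording and a different SPSS procedure (MIXED), with no new visits or data. The model is slightly more complex, assumes data are missing at random given the earlier scores, and does not help for participants who leave before the 3-month KOOS. If the sponsor prefers to keep the ANCOVA as primary, items 3 and 4 are the minimum, with the primary set stated as participants who have a 12-month KOOS4.

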#### ① Subjective assessments

The primary outcome, KOOS4 at 12 months, has been validated to be associated with knee symptoms and pain at baseline. Referenced to statistical methods in previous studies, an analysis of covariance (ANCOVA) will be performed to analyze the between-group difference using the baseline KOOS4 as the covariate for adjustment. For other subjective assessments included in the secondary outcomes, ANCOVA models will also be applied to analyze the between-group differences with adjustment for the corresponding baseline scores. Between group differences will be presented as mean, 95% confidence interval (CI), and P value. For an outcome with a statistically significant difference, the clinical significance should be evaluated by comparing the mean and 95% CI with the MCID.

#### ② Radiological evaluation

Although some studies have demonstrated that SNQ values may be normally-distributed and used Student t test for comparison, it should be noted that SNQ values are relative values (rather than absolute values such as KOOS and Tegner score) with high variability, while analyses of between-group differences by subtracting 2 quotients is not clinically meaningful (at least not determined for now). Therefore, the graft maturity (represented by the SNQ values averaged for the 2 radiological investigators) will be considered as ordinal variables and compared using the non-parametric test (Mann-Whitney-Wilcoxon test).

#### ③ Other variables

The Kolmogorov-Smirnov test will be applied to evaluate the normality for continuous variables. The Student t test will be used for comparison of continuous variables with normal distribution. The Mann-Whitney-Wilcoxon test will be used for comparison of non-normally distributed continuous variables and ordinal variables (including GROC, amount of ACL

remnant, and grades of knee laxity). The Pearson chi-square test or Fisher exact test will be used for comparison of categorical variables (including demographic data and adverse events), depending on expected frequencies for the contingency tables.

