#### **10.4 Secondary Outcomes: Physical Examinations**

① Knee range of motion, at each follow-up

The active-assisted range of motion is measured by placing the axis of a goniometer over the lateral femoral epicondyle and lining the two arms along the femoral and fibular axes, with positive values indicating knee flexion and negative values indicating hyperextension. The knee flexion and extension are assisted by both arms of the participant (in the sitting position) and a firm pillow beneath the heel (in the supine position), respectively.

② Knee circumference, at each follow-up

The knee circumference is measured by placing a tape measure circumferentially around the knee at the mid-patellar level while the participant is in the supine position with full knee extension. Results are presented as the side-to-side differences by subtracting the circumference of the contralateral knee, with higher positive values indicating worse swelling.

③ Knee laxity, at 12 months

The anterior drawer and Lachman tests are used to assess knee anteroposterior laxity at 90° and 30° of flexion by manual, respectively; grades include 0 (0–2 mm), 1 (3–5 mm), 2 (6–10 mm), and 3 (>10 mm). The pivot-shift test is used to assess knee rotatory laxity by manual; grades include 0 (negative), 1 (glide), 2 (clunk), and 3 (gross reduction). A KT-1000 arthrometer is used for quantitative measurements of anterior tibial translation at 30° of knee flexion, with higher results indicating increased knee anteroposterior laxity.

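### For range of motion, knee circumference and KT-1000, a normality test on the trial data picks the comparison, so method and effect measure can change between visits

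*Protocol*

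**What the plan says.** The rule stands in the protocol, Section 12.1, under Other variables. It opens with "The Kolmogorov-Smirnov test will be applied to evaluate the normality for continuous variables" and has two branches: "The Student t test will be used for comparison of continuous variables with normal distribution" and "The Mann-Whitney-Wilcoxon test will be used for comparison of non-normally distributed continuous variables and ordinal variables". The opening of Section 12.1 switches the descriptive summary on the same criterion: "mean and SD (for normally distributed values), median and interquartile range (for non-normally distributed values".

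Most outcomes are outside the rule:

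- KOOS4 at 12 months: "an analysis of covariance (ANCOVA) will be performed to analyze the between-group difference using the baseline KOOS 4 as the covariate for adjustment".
- The remaining subjective scores: "For other subjective assessments included in the secondary outcomes, ANCOVA models will also be applied to analyze the between-group differences".
- SNQ: these values "will be considered as ordinal variables and compared using the non-parametric test (Mann-Whitney-Wilcoxon test".
- GROC and the laxity grades are named as ordinal and go to the rank test without a screen.

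The continuous outcomes that remain come from Section 10.4. Range of motion ("The active-assisted range of motion is measured by placing the axis of a goniometer over the lateral femoral epicondyle") and knee circumference are taken at every follow-up. KT-1000 translation is taken at 12 months. Continuous baseline variables also fall under the rule.

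The protocol does not say whether normality is tested by arm or pooled, at each visit or once, at what threshold, or with which variant of the test. Nor does it give the recording step of the goniometer, tape or arthrometer.

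**The concern.** Swelling and adhesion are among the secondary purposes in Section 2, and circumference and range of motion are the measures that carry them. Under the rule, the data decide at analysis whether each is compared by means or by ranks. The two branches answer different questions. A reader following knee flexion from 4 weeks to 12 months could meet a mean difference at some visits and a rank comparison at others, with the switch caused by sampling noise in the normality test.

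Section 12.2 repeats all outcomes in a per-protocol set by the same methods. A changed result there could come from the change of test and not from the change of population.

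Both branches are also unadjusted, although Section 6.2 collects range of motion and circumference before surgery.

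**Working it through.** **Inputs from the protocol.** Section 5: 51 per group before dropout, 60 after, two-sided 0.05, effect size 13/20 = 0.65. Section 9: physical examinations at 4 weeks, 8 weeks, 3, 6 and 12 months, so five visits.

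**The plan's own figure.** It is used only to set n and is not disputed. By the noncentral t distribution, power is 0.896 at 50 and 0.902 at 51 per group, so n = 51. Then 51/(1 − 0.15) = 60. Both reproduce.

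**Assumed, because the protocol is silent.** Recording step, SD, shape of the distribution, test variant and correlation between visits. The range is shown for each.

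**Step 1: how often truly normal data are called non-normal.** Simulated rejection rates (20,000 per cell), with the recording step as a fraction of the SD:

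| n and variant | unrounded | 0.1 SD | 0.25 SD | 0.5 SD |
|---|---|---|---|---|
| 51, Lilliefors | 5.1% | 8.2% | 24.4% | 80.3% |
| 51, plain | 0% | 0% | 0.2% | 4.6% |
| 102, Lilliefors | 5.1% | 11.8% | 52.2% | 100% |
| 102, plain | 0% | 0% | 1.1% | 34.5% |

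Plain means the uncorrected critical value with estimated mean and SD. As a coarse example, take flexion with SD 12 read in 5-degree steps (5/12 = 0.42 SD). The rates are then 2% (plain) and 62.5% (Lilliefors) at n = 51, and 16.75% and 97% at n = 102.

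**Step 2: mixed tests over five visits.** If each visit is screened separately, rejects with probability p, and visits are independent:

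P(mixed) = 1 − p⁵ − (1 − p)⁵

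| p | Setting | P(mixed) |
|---|---|---|
| 0.02 | 5-degree, plain, n = 51 | 1 − 0.000 − 0.904 = 0.10 |
| 0.1675 | 5-degree, plain, n = 102 | 1 − 0.000 − 0.400 = 0.60 |
| 0.625 | 5-degree, Lilliefors, n = 51 | 1 − 0.095 − 0.007 = 0.90 |
| 0.97 | 5-degree, Lilliefors, n = 102 | 1 − 0.859 − 0.000 = 0.14 |
| 0.05 | exactly normal, Lilliefors | 1 − 0.000 − 0.774 = 0.23 |

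The relation is not monotone. A screen that nearly always or nearly never rejects gives a consistent test. With the plain variant and finely read normal data, p is near 0 and so is P(mixed).

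Independence is not essential. With one unchanged skewed (gamma) shape at all five visits, skewness 0.45 to 1.0, n = 51 to 60, latent correlation 0 to 0.7 and the Lilliefors variant, mixed tests occurred in 44% to 93% of simulated trials.

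**Step 3: per-protocol set.** With 10% of values removed at random (assumption) and the Lilliefors variant, the screen picked a different test in the reduced set in 3% to 17% of simulated trials. This covers normal, rounded and skewed data at n = 51 and n = 102.

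**Step 4: type I error of the whole two-stage procedure.** At 51 per arm with no effect, screening each arm and using the rank test if either fails, the error was 4.9% (normal) and 5.1% (gamma, skewness 0.82). The t test and the rank test gave different verdicts at 0.05 in 1.9% and 2.7% of trials. The t test alone gave 4.8% to 5.0% for rounded, skewed and zero-heavy data, so the screen is not needed to protect it at this size.

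**Step 5: unused baseline.** Adjusting for a baseline with correlation r multiplies the standard error by about √(1 − r²): 0.995 at r = 0.1, 0.954 at r = 0.3, 0.866 at r = 0.5. The protocol gives no r. For range of motion it may be low, because inclusion criterion ③ already restricts preoperative motion.

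**The case against.** The strongest reply is that nothing invalid has been shown. Both branches are valid tests, the two-stage procedure holds its error rate, and only three secondary measures are involved. The rounding results depend on a step that the protocol does not state, and a 5-degree step lies at the coarse end. The rule does not say that normality is checked visit by visit; if it were checked once per outcome, the test would not vary between visits. The software is named (IBM SPSS), so only the variant is open. Median and IQR are prescribed for non-normal variables, and nothing forbids a location-shift estimate beside the rank test.

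Much of this stands, and it rules out several stronger readings that a reader might infer:

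- **That every continuous outcome is affected.** Section 12.1 fixes the method for KOOS4, the other subjective scores and SNQ.
- **That false positives increase.** The simulated error is 4.9% to 5.1%.
- **That the screen mainly detects rounding, or that switching is the usual result.** Both depend on an undocumented step and variant, and the calculated range runs from near zero to about 90%.
- **That a rank result would come with no description of size.** Group medians would be reported. What the plan does not prescribe for that branch is a between-group estimate with a CI.

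What the reply does not answer is that the choice is left to the data and the rule for making it is incomplete. The same section already analyses the bounded subjective scores by ANCOVA without any screen.

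**Conclusion.** The point holds for range of motion, knee circumference and KT-1000 translation. Their test, summary and effect measure depend on a Kolmogorov-Smirnov result whose unit, timing, threshold and variant are not given. Where the screen is applied at each visit, mixed tests over the five visits of one outcome occur in about 10% to 90% of trials across the four 5-degree settings, and in about 23% for exactly normal data with the Lilliefors variant. Both figures assume independent visits; finely read data under the plain variant would give almost none. KT-1000 has a single visit, so it can switch only between analysis sets.

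The cost is in consistency, interpretability and some precision of secondary outcomes. The primary conclusion is untouched, and no material type I error inflation was found. This is a correction that should be made, not one on which the trial's validity turns.

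**What to change.** Delete the normality screen for these three outcomes and name the analysis in advance:

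- **Range of motion and circumference, every visit:** the ANCOVA already used for the subjective scores, with arm and the preoperative value of the same measure. Report the mean difference with 95% CI, using one robust standard error named beforehand. For circumference the covariate should be the preoperative side-to-side difference, to match the outcome in Section 10.4.
- **KT-1000 at 12 months:** one mean comparison with 95% CI, fixed in advance. Adjust only if a comparable baseline KT-1000 reading exists. Section 6.2 records baseline laxity under anesthesia and names no device, so this cannot be presumed.
- **Rank tests:** keep them for the outcomes already treated as ordinal (GROC, laxity grades, SNQ).
- **Median and IQR:** show them descriptively where useful, without letting them determine the test.

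With the method fixed, the chance of different tests across visits or analysis sets is zero. The cost is a change of wording. Range of motion and circumference are already measured before surgery; the one thing to confirm is that the contralateral circumference was recorded then as well.

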## **6.2 Baseline Evaluation**

- ① Demographic characteristics (self-reported, before surgery): age, gender, body mass index, affected side, Beighton score (hypermobility), preinjury Tegner score (sports level), types of sports participation at injury, and time from injury to surgery.
- ② Subjective assessments (in written forms, before surgery): Knee Injury and Osteoarthritis Outcome Score (KOOS), P4 score for pain, Lysholm score, and subjective International Knee Documentation Committee (IKDC) score.
- ③ Physical examinations: knee range of motion and knee circumference at the mid-patellar level (before surgery); knee laxity (under anesthesia, during surgery).
- ④ Surgical details: amount of ACL remnant, graft diameters (for anteromedial and posterolateral bundles), and meniscal treatment (none or meniscal resection).

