## **Section 8. Intervention and Control**

### **8.1 Intervention**

Participants allocated to the intervention group will receive blood withdrawal followed by PRP injection at 4 weeks ( $\pm 3$  days), 8 weeks ( $\pm 5$  days), and 3 months ( $\pm 7$  days) during the routine follow-up visits (after clinical assessments) following the standardized protocol:

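### Range of motion and knee circumference: the 4-week values precede the first injection but are listed as outcomes, and later visits are compared without baseline adjustment

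*Protocol*

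**What the plan says.** Protocol 10.4 lists knee range of motion and knee circumference as secondary outcomes, both "at each follow-up". The schedule in Section 9 has physical examinations at 4 weeks, 8 weeks, 3, 6 and 12 months.

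Protocol 8.1 places the PRP injections at 4 weeks, 8 weeks and 3 months, "during the routine follow-up visits (after clinical assessments". Protocol 7.2 has the participant learn the allocation at the first follow-up visit, which is the same 4-week visit.

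Protocol 6.2 also collects both measures before surgery, including "knee circumference at the mid-patellar level".

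For the analysis, 12.1 (Subjective assessments) plans ANCOVA on baseline KOOS4 for the primary outcome and extends it: "For other subjective assessments included in the secondary outcomes, ANCOVA models will also be applied", each with its own baseline score. Physical examinations fall under 12.1 (Other variables). There, "The Kolmogorov-Smirnov test will be applied to evaluate the normality for continuous variables"; then "The Student t test will be used for comparison of continuous variables with normal distribution", and "The Mann-Whitney-Wilcoxon test will be used for comparison of non-normally distributed continuous variables and ordinal variables". No covariate is named for these outcomes.

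**The concern.** Two features of the plan do not fit together.

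First, nobody has received PRP when range of motion and circumference are measured at 4 weeks. The protocol nevertheless counts these values among the outcomes to be compared between arms. A nominally significant difference there could be reported as early benefit or harm of a treatment not yet given.

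Second, the plan adopts baseline adjustment for the subjective scores but not for these two measures, and gives no reason. It does give a reason for handling the MRI signal quotients differently. A preoperative value and a 4-week pre-injection value are both collected, and neither is used.

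Swelling and adhesion are named in the secondary purposes (Section 2). The examiners are blinded, whereas the participants who self-report the primary outcome are not. These measures are therefore useful corroboration, and their precision is worth having.

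**Working it through.** **Timing.** Set side by side: 10.4 and Section 9 put the examination at 4 weeks; 8.1 puts the first injection at 4 weeks, after the assessments. So the order is examination, then injection. For the reveal of allocation, 7.2 gives only the visit, not its place before or after the examination.

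**The plan's own figure.** The protocol states no power for these outcomes. Its only sample size is for KOOS4: 13/20 = 0.65 SD, two-sided 0.05, power 0.90. The noncentral t calculation gives 51 per group (power 0.9016; 0.8958 at 50). Then 51/(1 − 0.15) = 60 per group. Both figures reproduce, and 60 per group is used below.

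**Tests at 4 weeks.** If the examination precedes the reveal, the true difference at 4 weeks is zero. Flexion, extension and circumference make three tests at 0.05. The chance of at least one significant result is 1 − 0.95³ = 0.143, about 14%, if they are independent (an assumption).

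**Precision at later visits.** Let r be the within-arm correlation between the 4-week and the later value. It is not in the documents; 0.3 to 0.7 is an assumed range.

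- Residual variance with ANCOVA = (1 − r²) × unadjusted variance.
- CI width ratio = √(1 − r²).
- With 60 per group, the unadjusted t test has 80% power for a difference of 0.516 SD. Adjusted power at that difference uses the noncentral t with effect 0.516/√(1 − r²) on 2 × 60 − 3 = 117 df.
- Difference detectable with 80% power after adjustment ≈ 0.516 × √(1 − r²).

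**Carried-over imbalance.** The standard error of a chance 4-week difference is √(2/60) = 0.183 SD, so its 95% range is ±1.96 × 0.183 = ±0.358 SD. Without adjustment, r times that difference passes into a later comparison.

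| | r = 0.3 | r = 0.5 | r = 0.7 |
|---|---|---|---|
| 1 − r² | 0.91 | 0.75 | 0.51 |
| CI width, adjusted/unadjusted | 95% | 87% | 71% |
| Power where unadjusted has 80% | 83.6% | 89.9% | 97.5% |
| Detectable difference (SD; 0.516 unadjusted) | 0.492 | 0.447 | 0.368 |
| Equivalent n per group, 60/(1 − r²) | 66 | 80 | 118 |
| Carried shift at the edge of the 95% range (SD) | 0.11 | 0.18 | 0.25 |

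With 51 per group, the power gains are the same, and the detectable difference goes from 0.560 SD to 0.534, 0.485 and 0.400 SD.

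**The case against.** The strongest reply is that nothing here is invalid. An unadjusted comparison of randomized arms is unbiased with the correct type I error, and its standard error already allows for chance imbalance. No power is claimed for these outcomes, and the primary outcome already has a baseline-adjusted ANCOVA. This stands, and it limits the point to efficiency and labelling in secondary outcomes.

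The size of the gain is also open. No document gives r, and it may weaken between 8 weeks and 12 months. Rehabilitation aims at full flexion at 4–6 months (6.4), so late range of motion may cluster near a ceiling, where r and a linear model could both suffer. Leaving out the preoperative value is partly defensible: eligibility requires nearly normal preoperative motion (4.1), which restricts that covariate. Circumference is already a side-to-side difference, which removes body size, though not the knee's own earlier swelling.

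A reader might infer that any 4-week difference is chance alone, so that the 4-week tests can yield only false positives. The documents do not establish this. Allocation is revealed at the same visit, and the order of reveal and examination is not stated. Range of motion is active-assisted, with the participant's own arms assisting flexion, so it can depend on effort. If the reveal comes first, a difference could reflect knowledge of allocation. It still could not reflect PRP.

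A reader might also infer that the Kolmogorov-Smirnov pre-test almost never rejects normality. That depends on a version the protocol does not specify. In simulations of one assumed skewed distribution (gamma with shape 4, n = 51), the uncorrected test rejected in 1.5% to 1.9% of runs and the Lilliefors-corrected test in about 41% to 42%. Nothing in the documents supports that skewness for these variables, so no conclusion is drawn about how the pre-test would perform.

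Finally, 12.2 allows multivariate regression. It is optional and exploratory there, and does not replace a planned adjusted comparison.

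**Conclusion.** The point holds as a modest improvement to secondary analyses. The 4-week range of motion and circumference values precede the first injection and should not be presented as efficacy results. Comparing later visits without adjustment gives up precision that data already collected could supply: under the assumed r of 0.3 to 0.7, the CI would be about 5% to 29% narrower. The lower end is a small gain, and the upper end should not be relied on.

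The figures assume a linear relation, the same r in both arms, complete data at 60 per group, and a 4-week value unaffected by knowledge of allocation. That last condition is one the protocol does not yet secure. The documents do not support a claim of bias or inflated type I error at later visits, and the primary conclusion is not affected.

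**What to change.** 1. In 7.2 and 8.1, state that the 4-week physical examination is completed before allocation is revealed to the participant.
2. In 10.4, label the 4-week range of motion and circumference as pre-injection baseline values, summarised by arm with no efficacy test.
3. In 12.1, take these two measures out of the unadjusted group. Analyse 8 weeks and 3, 6 and 12 months by ANCOVA, or by one mixed model over visits, with the 4-week value as covariate. Report the mean difference and 95% CI.
4. If the order in step 1 cannot be guaranteed, use the preoperative value as covariate instead, with circumference as the side-to-side difference defined in 10.4. Accept a smaller gain, because eligibility restricts preoperative range of motion.

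Fixing the model in advance makes the normality pre-test unnecessary for these outcomes.

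The cost is wording in 7.2, 8.1, 10.4 and 12.1, plus keeping to a set order at one visit. No new measurement and no change in sample size is needed.
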